### HbA1c

Glycated haemoglobin (HbA1c) will be measured by traditionally calibrated point-of-care instrument (DCA Vantage Analyzer, Siemens Healthcare Diagnostics, Ireland) at all sites, which meets acceptance criteria of having a total CV < 3% in the clinically relevant HbA1c range [33]. In the event a value is > 130 mmol/mol (> 14%, maximum reading possible) the value will be recorded as 130.

### isCGM glucose metrics

During all follow-up visits, all retrospective glucose readings from the previous 2 weeks will be downloaded from the isCGM reader or LibreView. Hypoglycaemia (time below target) will be recorded as percentage of time below target (< 3.9 mmol/L). Time in range will be recorded as the percentage of time in the range (3.9–10.0 mmol/L) [34, 35]. Hyperglycaemia (time above target) will be recorded as percentage of time above target (> 10 mmol/L). Glucose levels < 3.9 mmol/L between 10 pm and 7am (nocturnal hypoglycaemia) will be reported to the appropriate diabetes care provider for follow-up.

### Glucose monitoring behaviour

Glucose monitoring behaviour will be defined as scanning (intervention group) or SMBG (intervention and control group), which will be determined by device downloads of glucose monitoring device data.

### isCGM acceptability

isCGM acceptability will be evaluated using a non-validated instrument adapted from previous similar research [36]. On an ordinal scale from 0 (strongly disagree) to 5 (strongly agree), participants will rate their opinion regarding the following areas: acceptability of sensor application, wear/use of the device and comparison to SMBG.

### Psychosocial assessments

Psychosocial data and overall diabetes treatment acceptance will be collected through validated self-report questionnaires completed online using (REDCap Research Electronic Data Capture) software and the order of administration will be standardised to increase reliability. Together the questionnaires will take between 30 and 45 min to complete at each time point. All questionnaires will be administered in English. Clinical care teams will be notified if participants report physical or mental health problems necessitating follow-up.

The 33-item Pediatric Quality of Life Inventory (PedsQL) 3.2 Diabetes Module is a measure of diabetes-specific health-related quality of life that assesses participant’s and parent’s/guardian’s perceptions of the participant’s diabetes-specific symptoms and management challenges during the past month [37]. The PedsQL 3.2 Diabetes Module measures five domains: Diabetes Symptoms, Treatment Barriers, Treatment Adherence, Worry and Communication. Participant self-report forms are specific for ages 5–7, (young child), 8–12 (child), and 13–14 (adolescent). The parent proxy form is specific to ages 2–4 (toddler), 5–7 (young child), 8–12 (child), 13–14 (adolescent). The PedsQL 3.2 Diabetes Module Diabetes Symptoms and Diabetes Management Summary scores have demonstrated excellent measurement properties and are recommended as useful standardised patient-reported outcomes of diabetes symptoms and diabetes management in clinical research in children with type 1 diabetes [37]. Items are rated from 0 (never a problem) to 4 (almost always a problem). Item ratings are then reverse scored and linearly transformed to a 0–100 scale, with higher scores reflecting a better quality of life.

The Hypoglycaemia Fear Survey for Children (HFSC) is a 25-item instrument adapted from the adult HFS [38]. The HFSC will be completed by children aged 6 years and older. Overall, higher scores reflect greater fear of hypoglycaemia, a higher score on the Behaviour Subscale reflects a greater tendency to avoid hypoglycaemia and/or its negative consequences, and a higher score on the Worry Subscale indicates more worry concerning episodes of hypoglycaemia and its consequences. The CHFS has shown adequate internal consistency (HFSC behaviour subscale alpha = 0.70; CHFS worry subscale alpha = 0.89; and CHFS-Total alpha = 0.85) [38]. HFSC worry subscale and total scores have been shown to correlate significantly with other measures of anxiety [38]. Total scores and subscale scores will be calculated as z-scores standardised to the instrument-specific and baseline means and standard deviations.

The Self-Efficacy for Diabetes Self-Management (SEDM) is a 10-item self-report questionnaire for youth aged 10–16 years that examines confidence to carry out self-care behaviours and covers all the key areas of diabetes self-management [39]. The SEDM will be completed by participants who are 10 years and older. Participants are asked “How sure are you that you can do each of the following, almost all the time” and items are rated from 1 (not at all sure) to 10 (completely sure) and averaged. Higher scores indicate higher self-efficacy. The SEDM has demonstrated good validity and reliability (Cronbach’s alpha 0.9) [39].

At Visit 1, parents/guardians of enrolled participants who provide written consent for their own participation in the study will complete a short questionnaire collecting demographic characteristics (e.g., age, gender, education level, and ethnicity). At the baseline and follow-up visits parents/guardians will complete questionnaires to assess their perceptions of their own fear of their child experiencing hypoglycaemia using the parent version of the scale [38].

### Statistical analysis

A sample size of 88 (44 participants in each group) would provide 80% power to detect a difference in changes in HbA1c of 7 mmol/mol (0.75%) between the intervention and control group using standard deviation of 15 mmol/mol and correlation of 0.7 between repeated observations on the same person and a two-sided test at the 0.05 level [26, 40]. This is a clinically important difference and similar to other proven technologies such as insulin pumps or CGM. To account for a small amount of missing data and loss to follow-up, we will recruit a sample size of 100 (50 participants per group) at baseline.

The statistician will be blinded to allocation arm and will use non-informative group codes until all planned analyses are completed. Descriptive statistics will be calculated for all variables. The primary analysis will follow the intention-to-treat principle with all participants analysed in the group to which they were randomised, regardless of actual sensor wear. Additional analyses include: HbA1c, glucose monitoring frequency and adherence, episodes of moderate and severe hypoglycaemia (as defined in Safety section below), episodes of DKA, and psychosocial variables using Poisson and linear mixed models as appropriate. Statistical analysis will be performed using Stata software with two-sided p < 0.05 considered significant.

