### Control group

All participants will continue standard diabetes care from their usual paediatric diabetes care provider. Routine diabetes clinics are attended regularly (at least every 3 months) to provide diabetes care by a multi-disciplinary team (paediatric endocrinologist/diabetologist/paediatrician, diabetes nurse specialist, dietitian, psychologist). Between scheduled study visits, participants will have the usual ability to contact their clinical team as is routine for all patients. Control group participants will continue SMBG using conventional finger stick BG testing with a glucometer and be fitted with a blinded isCGM, sensor, which they will wear for the first and final 2 weeks of the RCT.

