### Intervention group

The intervention consists of a FreeStyle Libre 2 isCGM system (sensors, reader, USB cable, power adapter, user’s manual, and quick start guide) and structured education from trained research staff. Education will include sensor insertion, interpreting the readings, and optimisation of insulin dosages, if appropriate. The first sensor will be applied by research staff. Participants will insert the next sensor 14 days later under supervision (Visit 3) and for the remainder of the study. Participants will be instructed to scan a minimum of 6–10 times each day with no longer than 8 h between two scans. Research staff will set the initial recommended reader settings to 3.9 mmol/L (70 mg/dL) and 15.0 mmol/L (270 mg/dL). Research staff will access glucose data online through LibreView, a secure, cloud-based system, to generate a report of participants’ average interstitial glucose level, time above/in/below range, and scans per day at 2-, 4-, 8- and 12-weeks from isCGM commencement. If the report shows time spent 'low' is > 4% or time spent 'very low' is > 1% then the report will be forwarded to the participant's clinical team for follow-up.

As a safety precaution, participants will be instructed to perform SMBG to confirm their glucose level before therapeutic interventions or corrective action are taken if hypo- or hyperglycaemic levels (≤ 4.0 or ≥ 14.0 mmol/l) or symptoms occur.

To prevent sensor loss prior to the end of the 14-day sensor session, participants will be provided with either Rockadex (pre-cut sports tape), Hypafix® (BSN medical GmbH, Hamburg, Germany) or cohesive tape to be used to attach the sensor securely in the event the adhesive becomes loose.

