### Outcome assessments

The primary outcome is the between group change in HbA1c at 12-weeks (i.e., end of week 14 of study). The timing of all assessments is presented in Table 1. Trained research staff will be responsible for completing assessments. Visit 2 measurements will be taken before randomisation.

**Table 1 Tab1:** Outcome assessments

Assessment	Prior to randomisation	During RCT (Weeks 5, 7 & 11)	End of RCT	Ongoing
Demographics	*X*			
Anthropometry	*X*			
HbA1c	*X*		*X*	
CGM metrics	*X*	*X*	*X*	
Glucose monitoring behaviour	*X*		*X*	
isCGM acceptability			*X*	
Psychosocial assessments*	*X*		*X*	
Acute type 1 diabetes complications**				*X*

* Pediatric Quality of Life Inventory (PedsQL) 3.2 Diabetes Module, Hypoglycaemia Fear Survey (HFS), Self-Efficacy for Diabetes Self-Management (SEDM). ** Diabetic ketoacidosis, moderate and severe hypoglycaemia, issues related to glucose monitoring device use.

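### The statistician cannot stay blinded through every planned analysis, because scan counts and the week 7 and 11 CGM metrics exist in the intervention arm only

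*Protocol article*

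**What the plan says.** The protocol article, under Statistical analysis, states: "The statistician will be blinded to allocation arm and will use non-informative group codes until all planned analyses are completed". The same paragraph plans descriptive statistics for all variables and a set of further analyses: "Additional analyses include: HbA1c, glucose monitoring frequency and adherence, episodes of moderate and severe hypoglycaemia (as defined in Safety section below"), followed by DKA episodes and the psychosocial variables.

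The data behind these analyses are described elsewhere in the article:

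- Under Glucose monitoring behaviour: "Glucose monitoring behaviour will be defined as scanning (intervention group) or SMBG (intervention and control group").
- Under Control group, on the blinded sensor: "which they will wear for the first and final 2 weeks of the RCT".
- Under Intervention group: "Participants will insert the next sensor 14 days later under supervision (Visit 3) and for the remainder of the study".
- In Table 1, under Outcome assessments, the column headed "During RCT (Weeks 5, 7 & 11") carries a mark for CGM metrics and for nothing else.

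The Randomisation section says that participants, investigators and study staff are unmasked. The statistician is the only role described as blinded.

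**The concern.** Neutral group codes hide the allocation only while every variable the statistician sees could have come from either arm. A variable recorded in one arm only breaks the code as soon as it is tabulated. The article promises blinding to the end of all planned analyses while planning to analyse such variables.

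In an open-label trial this is the only masking left. What it protects are the analyst's choices: the form of the HbA1c model, the handling of missing values, and the treatment of extreme readings (the HbA1c section records values above 130 mmol/mol as 130). If those choices were made after arm-revealing data had been seen, the report would still claim blinding throughout, and the claim would be untrue.

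**Working it through.** No figure in the plan bears on the blinding claim, so the check traces which arm produces each planned variable.

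**1. Calendar.** Visit 1 opens week 1, and randomisation follows two weeks of blinded wear. The 12-week comparison therefore covers study weeks 3 to 14, which agrees with the article placing the primary outcome at the end of week 14 (2 + 12 = 14).

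**2. Sensor wear by arm.**

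- Control: first two weeks of the comparison (weeks 3–4) and last two (weeks 13–14).
- Intervention: weeks 3–14 without a break.

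**3. CGM metrics during the comparison.** The isCGM glucose metrics section says each follow-up download covers the previous two weeks. Taking a visit at either the start or the end of the named week:

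| Visit | Download window | Control sensor worn? |
|---|---|---|
| Week 5 | weeks 3–4 (start) or 4–5 (end) | Possibly, overlaps weeks 3–4 |
| Week 7 | weeks 5–6 or 6–7 | No |
| Week 11 | weeks 9–10 or 10–11 | No |

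Week 7 and 11 metrics can come only from the intervention arm. Week 5 metrics may exist in both.

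**4. Scan counts.** The article's definition gives scanning to the intervention group and SMBG to both groups. Controls continue finger-stick testing and their sensor is blinded. A table of scans by group code therefore has entries under one code only.

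**5. Are these variables within the planned analyses?** Monitoring frequency is named in the list of additional analyses, so scan counts fall directly inside the claim. Mid-trial CGM metrics are not named there. They enter through Table 1 together with the sentence on descriptive statistics for all variables.

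**6. Other candidates.**

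- *Hypoglycaemia episodes.* The Safety section looks for moderate and severe episodes in LibreView reports timed from the start of isCGM, which points to the intervention arm. Table 1, however, lists acute complications as ongoing without naming an arm, so other sources are possible.
- *Acceptability.* The instrument covers "acceptability of sensor application, wear/use of the device and comparison to SMBG". The article does not say which arm answers it.

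**7. Primary outcome.** HbA1c is measured before randomisation and at the end of the trial, on the same type of point-of-care analyser at all sites. It needs no device variable and does not reveal the arm by its presence or absence.

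**8. Sample size.** The plan's figure reproduces and is untouched by this point. The SD of change is 15 × √(2 × (1 − 0.7)) = 11.62. Then n = 2 × (1.96 + 0.842)² × 11.62² / 7² = 43.3, rounded up to 44 per group, or 88 in total.

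**The case against.** The strongest reply is that only a condensed article is at hand. The order of data release, the locking of the primary analysis and the handling of codes are commonly left to the full protocol or SAP, so silence on them is no fault. That stands. Nothing in the article says that the statistician receives one complete file, or sees device data before the HbA1c analysis is run. It does not rescue the sentence, however. No SAP can make blinding last through all planned analyses while the same statistician tabulates scans by code.

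A second reply is that scans and SMBG could be added into a single monitoring count before release, which would remove the empty cell for frequency. This is possible, but the article defines the two components by arm and plans to describe every variable.

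A third reply is that some device-related items need not reveal the arm. This also stands. All participants wear a blinded sensor before randomisation and controls wear one again during the trial, so controls could rate sensor application and wear. Controls' first two-week sensor may likewise supply week 5 data. A reader might infer that acceptability, week 5 CGM and every other device variable unmask the arms with certainty. The text does not establish that.

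**Conclusion.** The blinding claim is too wide as written. Scan counts alone are enough to defeat it, and the week 7 and 11 CGM metrics do so again if they are tabulated by code. Acceptability, week 5 CGM and LibreView-derived episodes may also reveal the arm, but the article leaves this open.

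A reader might go further and conclude that the primary HbA1c result is compromised, or that no order of analysis could protect it. The documents do not support either conclusion. HbA1c is collected alike in both arms, and its analysis can stay blinded if it is finished before arm-revealing data are seen. The risk is procedural, and no bias in any estimate has been shown.

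The conclusion assumes that one statistician carries out all the planned analyses, as the article's wording implies, and that scans are tabulated as a separate variable. In size it is a correction to one sentence plus a safeguard for the trial's only masking. It is worth making because it costs almost nothing.

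**What to change.** 1. **Narrow the claim.** State that the statistician is blinded for the primary HbA1c analysis and for other outcomes collected alike in both arms.
2. **First release.** Provide the arm code, site, HbA1c stratum, baseline covariates, baseline and 12-week HbA1c, and the questionnaires common to both arms. Include DKA and severe hypoglycaemia events only if they are ascertained in the same way in both arms. Finalise and lock these analyses.
3. **Second release, after the lock.** Provide scan and SMBG counts, CGM metrics, LibreView-derived hypoglycaemia episodes, acceptability, and device or skin events. Alternatively, give these data to a second analyst already on the team. SMBG counts belong here because they are analysed with scans, and a difference in finger-stick frequency could itself suggest the arm.

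The cost is one extra data extract and one reworded sentence. Sample size, alpha, power and trial procedures stay as they are.

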### Safety

For safety monitoring purposes, LibreView reports will be produced at 2-, 4-, 8-, and 12-weeks from isCGM commencement and checked for episodes of moderate (blood glucose values ≤ 3.9 mmol/L) and severe (child is having altered mental status and unable to assist in their care or is semiconscious or unconscious) hypoglycaemia. In the event the proportion of ‘low’ values is > 4% or ‘very low’ values is > 1% the report will be forwarded to the participant’s usual diabetes care provider for follow-up. Sensor failure rates and cutaneous adverse events (e.g., pain, itching, redness, subcutaneous haemorrhage, infection) will be self-reported to research staff at each visit or by phone call every four weeks throughout the study. All adverse events will be recorded in an Adverse Event form.

Participants will be asked to contact research staff immediately (by sending a photo of their affected skin site, if possible) if they notice a cutaneous issue associated with wearing the sensor. Clinical research staff will then advise if medical treatment is necessary. Participants will be referred to their general practitioner or emergency department, as appropriate, for management of medical events.

For more significant or persistent adverse events involving skin, a barrier product will be offered (e.g., Cavilon spray, SkinTac™) or drug therapy (e.g., zinc ointment, Fenistil gel, or hydrocortisone cream) prescribed, and the participant’s caregiver will be instructed to relocate the sensor to another area of the skin such that the effects are maintained at a tolerable level. Ultimately, the decision to continue or discontinue the use of the FreeStyle Libre 2 when localised skin symptoms occur will be made in consultation with the participant.

An internal Safety Monitoring Committee will be notified of severe adverse events (e.g., severe hypoglycaemia [BG value ≤ 3.9 mmol/L and resulting in loss of consciousness, a call for an ambulance and/or admission to hospital, or use of glucagon], DKA [being unwell due to hyperglycaemia and high ketones, and requiring a visit to the doctor, emergency room, or admission to hospital]) immediately after being reported to research staff. The Committee will then discuss any necessary action. Non-urgent events (moderate events) will be reported to the lead investigator after being reported to research staff. The internal Safety Monitoring Committee will be comprised of clinical investigators ([name]).

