### Randomisation

Prior to study commencement, a randomisation table was generated by a biostatistician using Stata 15.1 software and pre-defined parameters (pre-study HbA1c [58 to 74 mmol/mol, or ≥ 75 mmol/mol; 7.5 to 8.9%, or ≥ 9.0%], study site), and imported into the REDCap randomisation module. REDCap is a secure, web-based application designed to support data capture for research studies [27]. Participants will be randomised in a 1:1 ratio to either the control (SMBG) group or the intervention (isCGM) group at Visit 2 by research staff using the randomisation module. Participants, investigators, and study staff will not be masked to group allocation.

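### Moderate hypoglycaemia episodes are an analysed outcome, but the only stated data search for them is in the isCGM arm, so the between-arm count leans towards an apparent excess with isCGM

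*Protocol article*

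**What the plan says.** All references are to the protocol article.

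- **Statistical analysis** lists among the additional analyses "episodes of moderate and severe hypoglycaemia (as defined in Safety section below), episodes of DKA" and psychosocial variables, to be fitted with Poisson or linear mixed models.
- **Safety** defines a moderate episode by a blood glucose value of 3.9 mmol/L or below, with no symptom, duration or action required. Severe is defined by the child's clinical state. The section states that "LibreView reports will be produced at 2-, 4-, 8-, and 12-weeks from isCGM commencement and checked for episodes of moderate" and severe hypoglycaemia, and introduces this as safety monitoring.
- **Intervention group** gives the same 2-, 4-, 8- and 12-week LibreView schedule as part of the isCGM arm's procedures.
- **Control group** has controls continue finger-sticks and wear a blinded sensor, "which they will wear for the first and final 2 weeks of the RCT". No matching check of control data for episodes is stated.
- **Routes open to both arms:** Table 1 marks moderate and severe hypoglycaemia as ongoing collection, Safety has events reported to research staff, and Glucose monitoring behaviour has meter downloads in both arms, there to measure monitoring frequency.

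**The concern.** An episode defined only by a glucose threshold exists in the data only if glucose was sampled while it was low. A continuous sensor samples through the day and night; a finger-stick meter samples a few moments. If the arms are searched with these two instruments, the rate ratio mixes the treatment effect with the difference in detection.

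The direction is predictable: more episodes are found with isCGM. The trial could report a hypoglycaemia excess that does not exist, or lose a real reduction. Either would be a misleading safety statement about a device for children. Monitoring frequency is also something the intervention is meant to change, so the detection difference is tied to allocation and does not average out.

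**Working it through.** **1. The plan's own figure.** The only calculation stated is for HbA1c: "80% power to detect a difference in changes in HbA1c of 7 mmol/mol (0.75%) between the intervention and control group". Its inputs are an SD of 15 mmol/mol, a within-person correlation of 0.7 and a two-sided 5% test.

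- SD of change = 15 × √(2 × (1 − 0.7)) = 11.62 mmol/mol.
- With a difference of 7, this gives 44 per arm, and power at 44 per arm is 80.7%.
- 88 / (1 − 0.12) = 100.

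The stated 88 and 100 are reproduced. No figure is stated for hypoglycaemia, so nothing numerical in the plan is wrong here. The 44 per arm is carried forward.

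**2. Effect of unequal detection when there is no true difference.** Let *d* be the share of sensor-detectable moderate episodes that is found in controls. The documents do not give *d*, the mean count *μ* per child or the overdispersion *k*. They are assumptions: *d* from 0.4 to 0.8, *μ* from 6 to 40 over 12 weeks, *k* from 0.5 to 1.0.

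- Apparent rate ratio (isCGM / control) = 1/*d*.
- Var(log ratio) = (1/*μ* + *k*)/44 + (1/(*μd*) + *k*)/44.
- λ = ln(1/*d*) / √Var, and the chance of p < 0.05 is Φ(λ − 1.96) + Φ(−λ − 1.96).

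Example with *μ* = 20, *k* = 1, *d* = 0.6: Var = (1.050 + 1.083)/44 = 0.0485, SE = 0.220, λ = 0.511/0.220 = 2.32, and the chance of a false positive is 0.64.

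| Control detection *d* | Apparent ratio, no true effect | False-positive rate over the assumed *μ*, *k* | Appearance of a true ratio of 0.7 (0.7/*d*) |
|---|---|---|---|
| 1.0 | 1.00 | 0.05 | 0.70 |
| 0.8 | 1.25 | 0.16–0.30 | 0.875 |
| 0.6 | 1.67 | 0.58–0.91 | 1.17 |
| 0.4 | 2.50 | 0.97–1.00 | 1.75 |

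**3. Sensor days, if raw sensor counts were modelled without an offset.** The intervention arm could contribute 84 days (12 weeks) or 56 days (four reports of 2 weeks each, since isCGM glucose metrics describes 2-week downloads). Controls contribute 28 or 14 days, depending on whether their first 2 weeks are the pre-randomisation wear described under Procedures. The count ratio at equal true rates runs from 56/28 = 2 to 84/14 = 6. An offset removes this part. It does not remove the part in step 2, which arises from sampling within the day.

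**4. Whether the routes open to both arms equalise detection.** They do not. Background describes hypoglycaemia alarms on the device, and Intervention group sets the initial lower reader setting at 3.9 mmol/L. The same section tells isCGM families to confirm by finger-stick at 4.0 mmol/L or below. Reports to staff and meter readings in that arm are therefore prompted by the sensor close to the episode threshold. Controls find a low through symptoms or a test that happens to coincide with it.

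**The case against.** The strongest reply is that the link between LibreView and the outcome model is inferred. Safety describes those checks as monitoring, and Statistical analysis refers to that section for definitions; it does not name LibreView as the source of the counts. Episodes can also reach the database by routes not limited to one arm. This stands in part. It rules out saying that the false excess is certain or that LibreView is the sole source of events. It does not restore comparability, because the other routes are themselves sensor-prompted in one arm, and the only data search that the article describes is in that arm.

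Three stronger readings are tempting and are not supported:

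- *That severe hypoglycaemia and DKA are inflated too.* Both are defined by clinical state or consequences, so sampling density does not create them.
- *That the size is known.* Background mentions finger-stick testing six or more times daily. With 1-hour lows and tests unrelated to symptoms (both assumed), detection would be 6 × 1/24 = 25%, a ratio of 4.0. Symptoms prompt tests, so this is an extreme illustration. If only meter-confirmed values count, the contrast would be smaller.
- *That the trial has no fair measure of hypoglycaemia.* Percentage of time below 3.9 mmol/L is defined, Table 1 schedules CGM metrics at the end of the RCT, and controls wear a sensor in the final 2 weeks.

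**Conclusion.** The point holds for moderate hypoglycaemia episodes only. As the article stands, a threshold-only event is an analysed outcome, its one stated data search lies in the isCGM arm, and the remaining routes also detect more in that arm. The comparison would lean towards an apparent excess with isCGM.

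The direction follows from the documents; the size does not. For assumed control detection of 80% to 40%, a null effect appears as a ratio of 1.25 to 2.5, with a false-positive rate of about 0.16 to 1.00 depending on the assumed counts and overdispersion. A true 30% reduction would look like an increase at 60% detection.

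Blinding the statistician to allocation does not help, because the distortion is in the data. This is a secondary safety analysis, and a reader should not infer any fault in the HbA1c comparison or its sample size.

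**What to change.** - Base the between-arm comparison of moderate episodes on the final 2-week window in which both arms have sensor data. Use one threshold and one episode rule in both arms, and recorded sensor time as offset. Baseline blinded-sensor hypoglycaemia may be added as a covariate.
- State that the other LibreView checks are intervention-arm safety surveillance and do not enter the outcome. Follow-up of individual children is unchanged.
- Compare severe hypoglycaemia and DKA on clinically reported or recorded events, collected the same way in both arms. Procedures already takes the baseline history of these events from electronic medical records for all participants; repeating that check at the end visit would serve.
- State whether controls' first 2 weeks of sensor wear fall before or after randomisation.

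**Cost.** This is wording plus an end-of-study record check; the sensor data are already planned. Fewer moderate episodes enter the comparison: 14 of 84 days, so the assumed mean of 6 to 40 per child becomes 1 to 6.7. With equal detection and unchanged overdispersion, the standard error of the log ratio grows by √((6/*μ* + *k*)/(1/*μ* + *k*)). That is √(1.15/1.025) = 1.06 at *μ* = 40, *k* = 1, and √(1.5/0.667) = 1.5 at *μ* = 6, *k* = 0.5. That loss of precision is the price of a comparison made with sensor data in both arms.
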